## Statistical analysis

### Descriptive statistics

Descriptive statistics will be provided for all normally distributed variables in the form of mean scores (and standard deviations) before and after the intervention on each of the assessment instruments. Descriptive statistics of variables that are not normally distributed will be represented as median scores and ranges.

### Analysis

Differences in scores on every dependent variable are measured before and after the intervention and six months after the end of intervention. The significance of possible differences will be tested using logistic multileveling modeling
[56] with the subject and assessment time as levels and condition as independent variable. A model will be constructed for every dependent variable using the program MlwiN
[57]. Dummy variables will be constructed for every level and the statistical significance of the regression-effects will be tested using the T-test. The dummy-variables and their interactions will be added to the model as fixed effects.

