### Sample size calculation

Sample size was computed with a two-sided test using the IBM SPSS Sample Power program (Biostat, M. Borenstein), http://www.power-analysis.com/about_biostat.htm. The effect size of MERIT is not known. We chose to adopt the common convention in such instances, and set our effect size at 0.5
[34]. This is based on the consideration that should the effect size be lower, results would probably not be clinically relevant
[35,36]. In order to show medium effect sizes (0.5) with an alpha of 0.05 and a power of 0.80, a minimum of 48 subjects in both groups is required. This means that there is an 80% likelihood that the study will detect a statistically significant effect if such exists, and allows us to conclude that the mean metacognition score differs for MERIT versus TAU. Because this is a time consuming trial with people with a severe mental illness, we assume that the percentage of dropouts will be 20%. This means that for every 120 subjects enrolled in the study, 24 will be lost to follow-up or withdraw informed consent and will be excluded from the analysis. Therefore we will select 60 patients in the intervention group and 60 patients in the control group including 12 extra participants in each group to compensate for the anticipated missing data.

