#### Intake

**Diagnosis***M.I.N.I Plus Interview*[37]. This structured interview is used to confirm a diagnosis of schizophrenia or schizoaffective disorder. It is designed to detect Axis I diagnoses of the DSM IV-TR. The interview is divided into 26 sections; each section concerns a diagnostic category. At the end of every category the interviewer can determine whether the patient fulfills the diagnostic criteria for the diagnosis of the particular section.

#### 

**Metacognition***Indiana Psychiatric Illness Interview*[38]. This interview, which consists of five open questions, was developed with the goal of eliciting the life story and illness history of the patient. The MAS-A can be scored on the resulting transcript.

*Metacognition Assessment Scale*[10,11]. The MAS-A consists of four scales. The cutoff points for each scale: Selfreflectivity: below 5.5, Understanding the other’s mind: below 4.5, Decentration: below 2, Mastery: below 4.5. When the patient gets a score below cut off on three or more scales, metacognitive deficits are prominent and the patient meets the inclusion criteria.

#### 

**Symptoms***Positive and Negative Syndrome Scale*[39]. This structured interview consists of thirty items, each ranging from one to seven. The items fall into three subscales: positive symptoms, negative symptoms and general symptoms.

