**Work readiness***Work Readiness Questionnaire (WoRQ)*[48]. This questionnaire is filled in by the therapist of the client and has seven items designed to capture the patient's readiness to work as reflected by current capacity to initiate and maintain a useful activity. The items are rated to provide graded measurements, i.e., “strongly agree”, “agree”, “disagree” or “strongly disagree”. Next to these seven items it contains a final dichotomous work readiness judgment.

#### 

**Neurocognition***Nederlandse Leestest voor Volwassenen (NLV)*[49]. The NLV tests the pronunciation of irregularly spelled words and is used to determine premorbid intelligence.

*Trailmaking test A&B (TMT)*[50]. The TMT provides information on visual search, scanning, mental flexibility speed of processing and executive functions. It is part of the Halstead–Reitan Battery
[50]. The TMT consists of two parts. Part A requires an individual to draw lines sequentially connecting 25 encircled numbers distributed on a sheet of paper. Task requirements are similar for Part B except the person must alternate between numbers and letters (e.g., 1, A, 2, B, 3, C, etc.). The score on each part represents the amount of time required to complete the task
[51].

*Digit Symbol Test* (part of the Wechsler Adult Intelligence Scale
[52]). This test evaluates the recognition and recoding of visual information. The test consists of several rows of paired boxes with a digit in the top box and an empty space in the box below. At the top of the page is shown which symbols are paired to the digits. The participant has to fill in as many symbols in the empty boxes within 90 seconds.

#### 

**Cost-effectiveness***EuroQol (EQ-5D)*[53]. This questionnaire contains five scales: self care, mobility, usual activities, pain/discomfort and anxiety/depression. The participant has to rate his/her health as it is on the day of the interview, using five levels: “no problem” “slight problems” “moderate problems”, “severe problems”, “unable”/”extreme problems”
[54].

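### The only inferential model named is logistic, for every outcome, but the trial is powered on a difference in mean score and nearly all outcomes are numeric scales

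*Protocol article*

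**What the plan says.** The Analysis section of the protocol article gives one inferential method: "The significance of possible differences will be tested using logistic multileveling modeling". Subject and assessment time are the levels, and condition is the independent variable. The scope is general: "A model will be constructed for every dependent variable using the program MlwiN".

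The same paragraph describes the data and the test in terms that fit a numeric outcome. It opens with "Differences in scores on every dependent variable are measured before and after the intervention and six months after the end of intervention", and it says that "the statistical significance of the regression-effects will be tested using the T-test". Dummy variables and their interactions enter as fixed effects.

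Other sections also treat the outcomes as numeric:

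- **Sample size calculation:** the target is an effect size of 0.5, and the stated power "allows us to conclude that the mean metacognition score differs for MERIT versus TAU".
- **Descriptive statistics:** means with standard deviations for normally distributed variables, medians with ranges otherwise.
- **Intake and Assessment:** the MAS-A, PANSS, BCIS, IRI, QIDS-SR, ISMI and MANSA are rating scales, the Trailmaking test is timed, and the Digit Symbol test is a count within a time limit. The MAS-A cut-offs are given as an eligibility rule: "When the patient gets a score below cut off on three or more scales, metacognitive deficits are prominent".
- **Work readiness:** one element is expressly binary: "Next to these seven items it contains a final dichotomous work readiness judgment".

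**The concern.** A logistic model describes the odds of falling in a category. Its coefficients are log odds ratios, and none of them is a difference in mean score. The primary objective and the sample size both concern whether mean metacognition differs between MERIT and TAU, so the named model does not match the quantity that the trial was designed to estimate.

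This is more than a detail left to a fuller document. The article does state the primary test, and states it in a form that conflicts with its own sample size section. Left standing, it makes a sensible linear analysis look like a departure from the published plan. It would also let a categorisation chosen later, with no stated rule, claim to follow the plan.

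**Working it through.** **1. The passages side by side**

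| Place in the protocol article | Outcome type implied |
|---|---|
| Analysis, model named | Categorical (logistic) |
| Analysis, data described | Scores at three times |
| Analysis, test of effects | t-test of regression effects, usual for a linear model |
| Sample size calculation | Difference in mean metacognition score, d = 0.5 |
| Descriptive statistics | Means and SDs, or medians and ranges |
| Intake, Assessment | Mostly numeric scores, times, counts or ratings |
| Work readiness | One binary judgment |

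Only the first row calls for a logistic model across the board. No section defines categories for the scale scores. The sample size section does not name the MAS-A. That link is inferred from the inclusion criteria and the Intake section, but the powered quantity is a mean score whichever instrument is meant.

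**2. The plan's own figure**

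Inputs from the sample size section: d = 0.5, two-sided alpha 0.05, power 0.80, stated n = 48 per group, dropout 20%.

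- Two-means formula: n = 2(1.960 + 0.842)² / 0.5² = 62.8, so 63 per group (64 by the t-test). The stated 48 is not reproduced.
- Dropout step: 48 / (1 − 0.20) = 60 per group, 120 in total. This is reproduced.
- Power of a two-sample t-test with 48 per group: noncentrality 0.5 × √(48/2) = 2.449, 94 degrees of freedom, critical value 1.986, power 0.679.

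The gap between 48 and 63 or 64 is a separate matter. It matters here only because 0.68 is the reference power below.

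**3. Illustration: what one cut-point would cost**

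Assumptions, none of them in the document: normal scores with SD 1, a shift of 0.5, 48 per group, one time point, and a cut c SDs above the control mean.

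- p₁ = 1 − Φ(c) for control and p₂ = 1 − Φ(c − 0.5) for MERIT.
- SE = √{[p₁(1 − p₁) + p₂(1 − p₂)] / 48}.
- Power ≈ Φ[(p₂ − p₁)/SE − 1.960].

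| Cut c | p₁ | p₂ | Difference | SE | Power |
|---|---|---|---|---|---|
| 0 | 0.500 | 0.691 | 0.191 | 0.0982 | 0.496 |
| 0.25 | 0.401 | 0.599 | 0.197 | 0.1001 | 0.505 |
| 1 | 0.159 | 0.309 | 0.150 | 0.0850 | 0.422 |

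With a pooled variance under the null the three powers are 0.480, 0.490 and 0.410. Over a wider range of cuts, from 1 SD below to 1.5 SD above the control mean, the pooled figures run from 0.29 to 0.49.

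**4. If the scores were treated as ordinal instead**

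A rank test on five to nine categories, used as a stand-in for a cumulative logit under the same assumptions, has power of roughly 0.62 to 0.65 against 0.68. Little power is lost, but the estimate is still an odds ratio and not a mean difference.

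**The case against.** The strongest reply is that *logistic* is a slip. The paragraph speaks of scores and tests the effects with a t-test, the sample size section powers a mean difference, and no outcome is given a binary form. A team following the rest of the text would fit a linear model. That is probably right, and it is why the fix is cheap. It does not make the sentence correct, because the sentence is the only statement of the primary test.

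Four stronger readings are tempting, and the document does not support them:

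- **That every scale would have to be dichotomised.** The text does not say binary, and a logistic multilevel model can be ordinal. The power losses in the illustration are therefore one possible consequence and are not forced by the text.
- **That the model would break down at baseline because every included patient is impaired on the MAS-A.** The cut-offs serve eligibility only. Impaired versus not impaired is never proposed as an outcome.
- **That the WoRQ judgment is the only binary item.** The TiC-P also asks whether each type of care is used, which is a yes/no answer.
- **That the power figures forecast this trial's performance.** They rest on assumed cut-points and a single time point, whereas the plan has repeated measures.

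It is also fair to say that some outcomes, such as TiC-P counts and EQ-5D levels, are not strictly continuous. They are not all binary either, so a logistic model for every outcome remains wrong. How skewed outcomes are handled can be left to the analysis plan.

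**Conclusion.** The Analysis section is wrong as written. A logistic multilevel model for every dependent variable contradicts the powered mean-score comparison, the planned means and standard deviations, and the numeric outcomes, and it cannot estimate the difference in mean metacognition score. This conclusion rests on the text alone and needs no distributional assumption.

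The size of any power loss is conditional. If the score were dichotomised, power would fall from about 0.68 to about 0.50 with a cut near the control mean and to about 0.42 with a cut 1 SD above it, under the assumptions listed in the illustration. An ordinal model would lose much less. If the word is a slip and a linear model is fitted, no power is lost, but the published plan and the analysis would then disagree.

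**What to change.** In the Analysis section, replace the logistic model with a linear multilevel model (identity link, normal errors) for the MAS-A and the other scale scores. State the treatment effect as the condition difference at post-treatment and at follow-up, taken from the condition-by-time terms and reported in score units. Keep logistic multilevel models only for outcomes that are truly binary, such as the final WoRQ judgment and any yes/no TiC-P items that are analysed.

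The cost is a sentence or two of wording. The levels, the dummy variables, the interactions and the software can stay as they are, and no additional data are needed. The change should be recorded before outcome data are analysed, so that the linear model is the prespecified one.

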### Participants/setting

Participants in the study are people with schizophrenia or schizoaffective disorder and impaired metacognitive abilities. A total of 120 participants will be included from six mental health care institutions in the Netherlands. Thirteen therapists who work in these facilities will be trained to give the therapy.

Inclusion criteria are:

Impaired metacognitive skills, as measured by the Metacognition Assessment Scale (MAS-A);

Diagnosis of schizophrenia or schizoaffective disorder, according to DSM-IV-TR criteria;

Being able to give informed consent;

18 years or older;

No change in medication in the past thirty days.

Exclusion criteria are:

Acute psychosis (mean score of PANSS positive symptoms >4);

Co-morbid neurological disorder;

Substance dependence (not substance abuse as measured with the MINI Plus);

Impaired intellectual functioning (IQ <70)

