### Procedure

Thirteen therapists in six Dutch mental health care institutions will select all patients in their caseload that meet the inclusion criteria. They will answer four screening questions concerning these patients’ metacognitive abilities on a 10 point scale (see Section Screening for the screening questions). The therapists approach the patients that score below the cut-off of the screening and ask them if they are interested in participation. The names of the interested patients will be coded by the therapist. Out of these coded names a random selection will be chosen by the researchers to prevent selection bias. The selected coded names will be transferred back to the therapists, who will then provide the contact information of these patients to the researcher and will inform the patients that an assessor will approach them. The assessor will call the patient and answer any questions the patient may have about the study. Every participant has a two-week period to consider participation. If the patient is still willing to participate after this period, an assessor will make an appointment for an intake to confirm that the patient fulfills all of the study’s inclusion criteria. The intake will take approximately 1,5 hours. Patients that are included in the study will be randomly allocated to the treatment condition (MERIT) or treatment as usual (TAU). The randomization is conducted separately for each center and procedures will start directly after the first participants are included. Randomization will be done by a party independent from the trial research team. Results of the randomization process will be passed on to the onsite therapists. Block randomization will be used to ensure that the number of patients will be balanced over condition. Assessors will be blind to the subject’s condition. Rater blinding will be verified after the assessment. For therapists, it is of course not possible to be blind for condition. After assignment to intervention or control condition, the assessor plans a second appointment with the patient for baseline assessment. A research assistant, blind to treatment or control condition, who is not involved in the patient's treatment, will carry out this assessment. This assessment will take approximately 1.5 hours. Thereafter, the individual treatment will start. Onsite clinical psychologists that have partaken in the three-day MERIT training will provide the intervention. Participants in the control condition will receive treatment as usual (TAU). After forty sessions of treatment or forty weeks in the control condition, the assessment will be repeated (post-treatment). Follow-up assessment will take place six months after completion of the intervention.

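### The analysis model stops at subject and time, so differences between the thirteen MERIT therapists are left out of the standard error of the treatment effect

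*Protocol article*

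**What the plan says.** The Analysis section of the protocol article describes one model per dependent variable, "with the subject and assessment time as levels and condition as independent variable". It adds only this on further terms: "The dummy-variables and their interactions will be added to the model as fixed effects". Those dummies are built for the levels just named, so therapist and centre do not enter through them. Neither appears as a level, fixed effect or covariate anywhere else in the article.

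The design has both structures:

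- Centre: under Procedure, "The randomization is conducted separately for each center", with blocks.
- Therapist: under Participants/setting, "Thirteen therapists who work in these facilities will be trained to give the therapy". Under Procedure, "Onsite clinical psychologists that have partaken in the three-day MERIT training will provide the intervention". The therapy is individual, forty sessions per patient.
- Recruitment: under Procedure, "Thirteen therapists in six Dutch mental health care institutions will select all patients in their caseload that meet the inclusion criteria". Candidates therefore come from the therapists' own caseloads before anyone is randomised.

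The Sample size calculation section makes no allowance for clustering.

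**The concern.** Patients treated by the same therapist share whatever that therapist does well or badly. The article itself expects delivery to vary: the manual is target-driven rather than step by step, adherence is scored, and therapists are supervised every other week. A model whose highest level is the patient treats all MERIT patients as independent, which amounts to setting the between-therapist variance to zero.

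Two things are at stake. The p-value and confidence interval for MERIT against TAU would be somewhat too favourable. They would also describe these thirteen therapists only, whereas the Discussion looks ahead to MERIT as an addition to routine care, which is a claim about therapists in general.

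Centre raises a different question. It is the stratification factor, and the usual practice is to carry it into the analysis. Whether leaving it out affects the treatment standard error depends on which contrast in the repeated-measures model is the treatment effect.

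**Working it through.** **Inputs from the article.** Six centres, thirteen therapists, 60 patients enrolled and 48 evaluable per arm. The calculation is two-sided ("Sample size was computed with a two-sided test"), with targets given as follows: "In order to show medium effect sizes (0.5) with an alpha of 0.05 and a power of 0.80".

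**The plan's own figure.** The dropout step reproduces: 48 / (1 − 0.20) = 60. The 48 does not: for d = 0.5, two-sided alpha 0.05 and power 0.80, the requirement is 63 per arm (normal approximation) or 64 (t-test), and 48 per arm gives about 68% to 69% power. That is a separate matter. It is relevant here only because there is no spare power to absorb clustering.

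**Assumed input.** The therapist ICC, taken as 0.01, 0.05, 0.10 and 0.15. It means the therapist share of MERIT-arm variance in whatever quantity the treatment effect is measured on. Total variance is taken as equal in the two arms, with clustering in the MERIT arm only.

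**Therapist omitted.**

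- Evaluable patients per therapist: m = 48/13 = 3.69.
- MERIT-arm design effect: DE = 1 + (m − 1) × ICC.
- Variance of the difference relative to the model's: v = (DE + 1)/2.
- Correct standard error over model standard error: √v.
- Actual error rate of a nominal 5% test: 2 × [1 − Φ(1.96/√v)].

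| ICC | DE | v | √v | Actual error rate |
|---|---|---|---|---|
| 0.01 | 1.027 | 1.013 | 1.007 | 5.2% |
| 0.05 | 1.135 | 1.067 | 1.033 | 5.8% |
| 0.10 | 1.269 | 1.135 | 1.065 | 6.6% |
| 0.15 | 1.404 | 1.202 | 1.096 | 7.4% |

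If all 60 per arm were analysed, m = 60/13 = 4.62 and the error rates become 5.2% / 6.1% / 7.1% / 8.2%. A simulation of 20,000 trials (thirteen therapists in six centres, 48 per arm, two-sample t-test at one time point) gave 5.7% at ICC 0.05 and 6.7% at 0.10, in line with the formula.

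**Power (normal approximation, 48 per arm).** Without clustering it is 0.688. With ICC 0.05 / 0.10 / 0.15, the model as stated still rejects with probability 0.682 / 0.677 / 0.672. A test with the correct standard error has power 0.659 / 0.633 / 0.608.

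**Centre omitted.** There are two readings of the treatment effect.

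1. Condition-by-time interaction. Stable centre differences are absorbed by the subject intercept and cancel from change. In simulated complete data (six centres, 48 per arm, three visits, centre 10% of variance, random subject intercept) the interaction estimates were identical with and without five centre dummies, and so was their standard error: 0.20395 in both fits. Only the condition main effect, the baseline difference, changed, from 0.199 to 0.191.
2. Post-treatment difference at one time point. Ignoring a centre share of 5% makes the correct standard error √0.95 = 0.975 times the model's, and the error rate falls to 4.4%. In the same t-test simulation, centre 0.05 with therapist 0.05 gave 5.3%, and centre 0.05 with therapist 0.10 gave 5.8%. The two omissions partly offset.

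**The case against.** The strongest case against the point has four parts.

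**A condensed article may leave covariates to an analysis plan that is not shown.** This holds in part for centre: naming the levels does not rule out centre as a covariate. It does not hold for therapist. The article lists the levels of the model, and that list is too short for the design described.

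**TAU patients may belong to the same therapists.** This stands as a limit on size. Candidates come from the therapists' caseloads, so both arms may be linked to the same thirteen people. Therapist effects common to both arms then largely cancel, and only therapist-by-condition variance inflates the standard error. The tabulated rates assume clustering in MERIT only.

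**The ICC is assumed.** This also stands. At 0.01 the excess is trivial, and the documents support no particular value.

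**Centre and power.** A reader might infer that omitting centre overstates the treatment standard error by 3% to 5% and costs 2 to 5 points of power. The documents do not support that. Those figures belong to a comparison at a single time point, whereas the Analysis section describes repeated measures with interactions. Under the condition-by-time reading, which is natural though not spelled out, centre main effects leave the treatment standard error unchanged. A reader might also infer that the stated model loses power, from about 68% to about 65%, 62% or 60%, through therapist clustering. It does not: its rejection rate under the alternative barely moves. A loss of that order belongs to the corrected test, and is the price of sizing it properly.

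**Conclusion.** The point holds for therapists and is modest in size. The stated model has no term for a source of variation that the design creates, and the error runs in the anti-conservative direction. With 48 evaluable per arm, clustering in MERIT only and an assumed ICC of 0.01 to 0.15, the nominal 5% test runs at about 5.2% to 7.4%. It is closer to 5% if the arms share therapists or if stable centre differences offset it. That offset depends on unknown variances and on the single-time-point reading, so it is not a reason to leave the model as it is.

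For centre, the conclusion is limited to consistency between randomisation and analysis. No loss of precision is shown under the condition-by-time reading. It would be too strong to say that the standard errors are known to be materially wrong, because the documents give neither a therapist nor a centre variance.

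**What to change.** - Add a therapist-level random effect that acts on the post-baseline treatment effect, since therapy starts only after the baseline assessment. Use a partially nested form (MERIT arm only) if TAU patients have no link to these therapists. Use a random condition-by-time slope by therapist if they do.
- Use small-sample degrees of freedom suited to thirteen therapists with about four patients each.
- Include centre as a fixed effect together with its interaction with time. Main-effect dummies alone gain precision only if the treatment effect is a post-treatment difference, so say which contrast is the treatment effect.
- State in the sample size section that the power calculation ignores therapist clustering, or give power for a stated ICC.

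The cost is wording in the protocol or analysis plan, settled before unblinding, plus a record of which therapist each patient is linked to. The named software is built for multilevel models. The downside is real: if therapists differ, the interval is somewhat wider and the correctly sized test has less power (0.659 / 0.633 / 0.608 against 0.688 at ICC 0.05 / 0.10 / 0.15). The therapist variance will also be imprecisely estimated from thirteen clusters.

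### As described, the model leaves the baseline difference between arms free and omits centre; adjusting for pre-randomisation baselines and adding centre costs almost nothing, with a gain that depends on an unstated correlation

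*Protocol article*

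**What the plan says.** The Analysis section of the protocol article treats all three assessments as outcomes: "Differences in scores on every dependent variable are measured before and after the intervention and six months after the end of intervention". It describes a multilevel model with subject and assessment time as levels and condition as the independent variable, and adds: "The dummy-variables and their interactions will be added to the model as fixed effects". It mentions neither a baseline covariate nor equal baseline means across arms, and it has no centre term.

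On allocation, the Procedure section says: "The randomization is conducted separately for each center and procedures will start directly after the first participants are included". Blocks are used, and there are six institutions.

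Table 1 places the MAS, the interview it is scored from (IPII) and the PANSS at intake, before randomisation. The other repeated measures are first taken at a baseline visit that the Procedure section schedules after allocation.

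The Sample size calculation section takes an effect size of 0.5 and states: "with an alpha of 0.05 and a power of 0.80, a minimum of 48 subjects in both groups is required". It enrols 60 per arm to allow for 20% dropout. It mentions no correlation between baseline and post-treatment scores and no centre effect.

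**The concern.** If condition, time and their interaction are all free fixed effects and baseline is one of the responses, the post-treatment interaction term compares change from baseline between arms. Each arm then has its own baseline mean, although randomisation makes these means equal in expectation for anything measured beforehand. Estimating a difference known to be zero in expectation adds variance to the treatment effect. Nothing is gained in return for MAS-A, the instrument that measures the primary target, or for PANSS.

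Leaving out the factor by which randomisation was stratified is a separate, smaller mismatch. Stratifying balances centres across arms, but a model without centre still counts variation between centres as residual error. The reported standard error is then somewhat too large.

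What is at stake is precision on the primary outcome. The test remains valid.

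**Working it through.** **Inputs from the protocol article (Sample size calculation).** d = 0.5, two-sided alpha 0.05, 48 analysed per arm. **Assumed, because the documents give no value:** the baseline-to-post correlation r, the ratio of baseline to post-treatment SD, and the share of outcome variance lying between centres. Scores are treated as continuous, as that section does when it refers to a difference in mean score.

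**1. The plan's own figure.** For a plain two-sample comparison the noncentrality is 0.5 × √(48/2) = 2.449. Two-sided power is 0.688 by the normal approximation and 0.679 by noncentral t with 94 df, not 0.80. Reaching 0.80 takes 63 (normal) or 64 (t) per arm. The dropout step is correct: 48/0.8 = 60. So the figure of 48 is not reproduced as a two-sided calculation. That is a separate matter, but it means that the design has no spare power.

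**2. Free versus adjusted baseline, equal SDs.** In units of the post-treatment variance, the variance factor for the post-treatment contrast is:
- free baseline (difference in change): 2(1 − r);
- baseline as covariate, or equal baseline means: 1 − r².

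The ratio is (1 − r²)/[2(1 − r)] = (1 + r)/2, so the proportional reduction is (1 − r)/2. This is positive for every r below 1.

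| r (assumed) | 2(1 − r) | 1 − r² | Variance reduction | Power, free | Power, adjusted |
|---|---|---|---|---|---|
| 0.2 | 1.60 | 0.96 | 40% | 0.48 | 0.70 |
| 0.3 | 1.40 | 0.91 | 35% | 0.54 | 0.72 |
| 0.5 | 1.00 | 0.75 | 25% | 0.68 | 0.80 |
| 0.7 | 0.60 | 0.51 | 15% | 0.88 | 0.92 |
| 0.8 | 0.40 | 0.36 | 10% | 0.97 | 0.98 |

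Power is by noncentral t, with 94 df (free) or 93 df (adjusted).

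**3. If selection narrows the baseline SD.** Intake MAS-A is both the entry criterion and the baseline. Selecting on it shrinks the baseline variance but leaves the regression slope b of post on baseline unchanged. The variance of change is then the residual variance plus (1 − b)² × baseline variance, so the penalty for a free baseline shrinks with the baseline variance.

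Illustration (assumed): unselected SDs of 1, normal scores, lower half kept on baseline. The baseline variance falls to 1 − 2/π = 0.363.
- Unselected r = 0.5: residual 0.75; change 0.75 + 0.25 × 0.363 = 0.841; reduction 0.091/0.841 = 11%. The observed r is 0.33, where the equal-SD formula would give 34%. With d = 0.5 in post-treatment SDs of those selected, power is 0.68 free and 0.73 adjusted.
- Unselected r = 0.3: residual 0.91; change 1.088; reduction 16%.
- Unselected r = 0.7: residual 0.51; change 0.543; reduction 6%.

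Actual entry requires scores below cut-off on at least three of four subscales, so this shows direction and rough size only.

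**4. Centre.** Five further df change the adjusted power by less than 0.1 percentage point (at r = 0.5, 0.7993 with 93 df and 0.7988 with 88 df). In a simulation with six centres, 8 per arm in each and 4,000 runs per setting, adding centre after baseline adjustment changed power by about 0 to 1 point when centres explained 5% to 10% of variance. If centres explain 5% of the variance of the analysed quantity (assumed), the true two-sided error without centre is 2[1 − Φ(1.96/√0.95)] = 0.044. At 10% it is 0.039.

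**The case against.** The strongest objection is that the Analysis section is one condensed paragraph. It does not write out the parameterisation, and an article may leave covariates and stratification terms to the full plan. A longitudinal model with condition-by-time terms is also valid and unbiased under randomisation, so this is a question of efficiency. All of that stands. The free baseline is the natural reading and not a stated choice, and the missing centre term would be a weak point alone. But the article does give levels, predictor, fixed effects, software and test, and what it gives does not use the design.

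Three stronger readings are tempting, and the documents do not support them.
- A reader might infer that the low MAS-A entry rule lowers r and so makes the free-baseline model perform especially badly. Step 3 of the working shows the reverse: with selection on baseline, the loss from leaving it free is smaller than the equal-SD table suggests at the same observed r.
- A reader might infer that adjustment recovers most of the power missing from the sample size calculation. That depends on r. With equal SDs and starting from 0.68, adjustment closes more than half the gap to 0.80 only if r exceeds about 0.36. At r = 0.3 it reaches 0.72. Above r of about 0.63 the free-baseline contrast already exceeds 0.80. In the selection illustration, adjusted power ran from 0.69 to 0.80.
- A reader might infer that omitting centre costs real power or invalidates the test. It does neither to any important degree; the error is on the conservative side.

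It is also fair to object that the remedy does not reach every outcome. Measures first taken after allocation need the extra assumption that knowledge of the arm did not affect them, most plainly the work readiness questionnaire, which the unblinded therapist completes. The point is therefore limited to MAS-A and PANSS.

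**Conclusion.** The point holds as an efficiency matter of moderate weight. On its natural reading, the described model estimates a baseline difference that randomisation sets to zero in expectation for MAS-A and PANSS, and it omits the stratification factor. The direction of the gain from adjustment does not depend on r; the size does. With equal SDs, the variance reduction is 35% at r = 0.3, 25% at r = 0.5 and 15% at r = 0.7. With a narrowed baseline SD it is nearer 6% to 16% in the illustration. These figures rest on assumed correlations and SDs and apply to a single post-treatment contrast with 48 analysed per arm. Adjustment should not be presented as a repair of the sample size calculation. Centre is justified by consistency with the randomisation, not by power.

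**What to change.** Reword the Analysis section for MAS-A and PANSS in one of two ways:
- keep baseline as a response, but constrain its mean to be equal across arms: drop the condition main effect at baseline and keep condition-by-post and condition-by-follow-up; or
- use baseline as a covariate, with only post-treatment and follow-up scores as responses.

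Add five dummies for the six centres to the model. Do not apply the equal-baseline constraint to outcomes first measured after allocation unless their baseline is moved ahead of randomisation or the extra assumption is stated and defended. If a power gain is quoted, give it over a range of correlations and SD ratios.

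The cost is a change of analysis wording, five degrees of freedom for centre and one for a baseline covariate. No extra patients or measurements are needed.
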